#### A1: resource utilization and cost of illness associated with high risk of stroke and bleeding in patients with AF

2.4.1

In the SHI patient database, ICD-10 diagnostic codes will be used to select high-risk AF patients from AF patients without high risk of bleeding and stroke for the cost analysis in module A1 (see section “SHI study population”). A patient's index quarter, regardless of later being allocated to the high-risk group or not, will be the quarter in which the SHI patient inclusion criteria are fulfilled for the first time in the pre-observation year. In addition to these criteria (also using ICD-10 diagnosis codes^6^), patients will be allocated to the high risk of bleeding and stroke group if they have a CHA_2_DS_2_VASc-Score ≥ 2 and one of the following: a HAS-BLED value of ≥3, a diagnostic code for other non-traumatic intracranial hemorrhage, gastrointestinal bleeding, hematuria, bleeding from the respiratory tract, or chronic kidney disease in the observation period. Applicable ICD-10 codes to assess these indications were selected in cooperation with the CLOSURE-AF investigators.

Hierarchically regularized entropy balancing (39, 40), a method for statistical matching, will be used to ensure similar characteristics in terms of age, gender, morbidity (Charlson comorbidity index), and healthcare costs between the high-risk group and the control group without the high risk at baseline.

The two patient groups will be descriptively characterized; location and dispersion measures will be compared with respect to the distribution of appropriate metric variables such as age, morbidity indices, and bleeding risk. Frequencies will be reported for ordinal variables. Differences in mean values for dependent variables, such as resource utilization and direct and indirect costs, will be analyzed by performing a bilateral significance test of independent samples depending on the specific variable distribution in the actual data. The analysis will be conducted by a difference-in-difference design, carried out as two-way fixed effects regression model, alleviating further unobserved structural differences between both groups that may remain after balancing.

The analysis covers SHI data on medical, outpatient hospital and rehabilitation services, inpatient care, drug expenditures, medical aids (e.g., electrostimulation devices and blood pressure monitors), and disability benefits. Indirect costs will be measured by incremental unemployment days and average employee compensation in Germany in the corresponding calendar year, as indicated by the Federal Statistical Office (41).

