#### SHI study population

2.3.1

The SHI population for EvaClosure is selected from the data pool of a German statutory health insurance fund that comprises over 3 million insured persons. EvaClosure uses data from the years 2015 to 2021. Patients are selected if they
are 18 years or older, andhave a diagnosis code (of the 10th revision of the International Statistical Classification of Diseases and Related Health Problems; ICD-10) for AF documented in at least two different quarters during the baseline period (I48.0, I48.1, I48.2, I48.9)Patients are excluded from the sample in case of
discontinuous data coverage (e.g., due to interrupted insurance periods or change of health insurance fund)an absolute contraindication for ASA (an ICD-10 code for gastric or duodenal ulcers (K25.- or K26.-) or a prescription for methotrexate [Codes within the Anatomical Therapeutic Chemical Classification System (ATC): L01BA01 or L04AX03])previous heart transplant (code within the German Operation and Procedure Classification System; OPS: 5–375)malignant neoplasm of the heart, mediastinum, and pleura (ICD: C38.-) orpregnancy, birth, or postpartum diagnosis in the baseline period (ICD: O–.—)Patients are assigned to the high-risk group if in the baseline period they additionally have the following characteristics:
CHA_2_DS_2_VASc-Score ≥ 2, andhigh risk for bleeding, i.e., if at least one of the following criteria are met:
○HAS-BLED value of ≥ 3, or○an ICD-10 code for other non-traumatic intracranial hemorrhage (I62.-), or○gastrointestinal bleeding (K92.2), or○hematuria (R31), or○bleeding from the respiratory tract (R04.-), or○chronic kidney disease (N18.4)From the high-risk patients, the LAAC intervention group is selected using the following inclusion criteria:
Diagnosis-related group (DRG): F95A (interventional septal occlusion, age < 18 years, or atrial appendage occlusion) andOPS code 8-837.s0 (since 2016) or 8-837.s (before 2016)The control group (best medical care group) is also selected from the group of high-risk patients, defined by the following criteria:

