#### SHI data collection

2.3.2

SHI patient data are transferred for each year for the time period from 01.01.2015 to 31.12.2021; for each patient included, at least one year of baseline data (used to confirm inclusion/exclusion criteria prior to observation period) and at least two years of follow-up data are captured. The data include information on
sociodemographic characteristics (age, gender, and insurance period)outpatient medical care [diagnoses (ICD-10), quarter of diagnoses, procedures, costs of care]pharmaceuticals (dispensed drugs, numbers of packages, prescription date, dispense date, and costs of therapy)medical devices and allied health services (type of therapy or device, service provider, and therapy duration and costs)unemployability (diagnoses, sick leave durations and payments, and durations), andinpatient medical care: main and secondary diagnoses (ICD-10) upon discharge, surgeries and procedures (OPS), date and cause of admission, date and reason for discharge, and DRG code.

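### Module A1 dates high-risk status from the observation period, whereas section 2.3.1 dates it from the baseline period; under A1's wording, events in follow-up define the group whose follow-up costs are the outcome

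*Protocol article*

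**What the plan says.** All references are to the protocol article.

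- **Section 2.3.1 (SHI study population).** Patients "are assigned to the high-risk group if in the baseline period they additionally have the following characteristics": a CHA2DS2-VASc score of at least 2, plus at least one bleeding-risk criterion (HAS-BLED of at least 3, or one of several diagnosis codes).
- **Section 2.4.1 (module A1).** It points to section 2.3.1 and repeats the same criteria, but the list ends with "gastrointestinal bleeding, hematuria, bleeding from the respiratory tract, or chronic kidney disease in the observation period".
- **Section 2.3.2 (SHI data collection).** Each patient has at least one year of baseline data, "used to confirm inclusion/exclusion criteria prior to observation period".
- **Section 2.4.1, index quarter.** The index date is set in the same way for both groups: "regardless of later being allocated to the high-risk group or not, will be the quarter in which the SHI patient inclusion criteria are fulfilled", taking the earliest such quarter in the year before observation.
- **Section 2.4.1, balancing.** Entropy balancing is to make the groups similar in gender and age and to align "morbidity (Charlson comorbidity index), and healthcare costs between the high-risk group and the control group without the high risk at baseline".
- **Section 2.4.1, estimator.** "The analysis will be conducted by a difference-in-difference design, carried out as two-way fixed effects regression model".
- **Section 2.4 and Table 2.** A1 is a cost-of-illness study of high-risk status, covering one year before inclusion and four years after it.

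**The concern.** Group membership in A1 has two incompatible definitions, and the choice between them changes what is estimated.

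If status comes from the observation period, the exposure is read off the same years in which costs are counted. A patient without a criterion at baseline becomes high risk by having a bleed in follow-up, and the inpatient cost of that bleed is part of the outcome. The comparator meanwhile loses patients who had such bleeds, provided they also meet the stroke-score criterion. The result mixes the cost of being at high risk with the cost of having had the event.

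If status comes from the baseline period, that circularity goes, but a smaller question appears. The only pre-period is then a year in which the patient is already high risk. Matching comparators to that year's cost level selects unusually expensive comparators and hides part of a lasting excess, although A1's aim is the level of cost attached to high-risk status.

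**Working it through.** The article gives no cost figure for A1, so there is no stated result to reproduce. The first step is textual. The other two are illustrations on assumed inputs.

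**Step 1: are the windows really different?** Section 2.3.1 uses the baseline period and section 2.4.1 the observation period. Section 2.3.2 has baseline data confirm eligibility ahead of the observation period, and section 2.4.1 itself speaks of a pre-observation year and of later allocation to the high-risk group. These are two successive windows, not two names for one. In section 2.4.1 the time qualifier could attach to the whole list or only to its last item. Either way, at least one criterion is dated in the observation period, and none is dated at baseline.

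**Step 2: observation-period reading.** Assume 20% of patients have a qualifying event in follow-up, unrelated to anything at baseline, and that it adds E units to post-index cost. Nothing known at index distinguishes the groups, so a status fixed at index has an excess of 0. Simulation with 400,000 patients, entropy balancing on mean pre-year cost and then DiD gives:

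| E | Estimated excess |
|---|---|
| 0.5 | 0.50 |
| 1 | 1.00 |
| 2 | 2.01 |

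The whole event cost is returned as excess. Balancing and differencing do not remove it, because it arises after index.

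**Step 3: baseline reading.** Let m be the comparator's mean cost in both periods, D0 and D1 the high-risk group's excess before and after index, and r the within-group correlation of pre and post cost. Assume equal variances and a linear relation, so the regression slope of post on pre is r.

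- High-risk means: m + D0 before, m + D1 after.
- Comparator reweighted to the high-risk pre-year mean: m + D0 before, m + r × D0 after.
- Post-index difference: D1 − r × D0.
- Pre-year difference: 0, so DiD subtracts nothing further and also equals D1 − r × D0.
- For a constant excess D0 = D1 = D, the estimate is D × (1 − r), a loss of share r.

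Simulated results with 400,000 patients per group and a true post-index excess of 1 unit:

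| r (assumed) | Constant excess, DiD without cost balancing | Constant excess, DiD with cost balancing | Pre-year excess 1.5, with cost balancing | No pre-year excess, with cost balancing |
|---|---|---|---|---|
| 0.2 | 0.00 | 0.80 | 0.70 | 1.00 |
| 0.4 | 0.00 | 0.60 | 0.40 | 1.01 |
| 0.5 | −0.01 | 0.49 | 0.25 | 1.00 |
| 0.6 | 0.00 | 0.40 | 0.10 | 1.00 |
| 0.8 | 0.00 | 0.20 | −0.20 | 1.00 |

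The balanced columns agree with the formula; for example 1 − 0.5 × 1.5 = 0.25, and 1 − 0.8 × 1.5 = −0.20. The 1.5 column represents a pre-year peak because the qualifying event falls there. The last column shows that nothing is lost when there is no excess before index. The second column shows why dropping cost balancing while reporting only DiD would not help: a constant excess then cancels completely.

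**The case against.** **The later allocation may be intended.** A1 could be meant to follow patients who become high risk after index, for whom a clean pre-year and DiD are natural. That is a coherent design, but it is not what section 2.3.1 says. The index quarter is also tied to meeting the AF inclusion criteria, not to becoming high risk, and the qualifying event's cost would still sit in the outcome.

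**Section 2.3.2 speaks only of inclusion and exclusion criteria.** This is correct. Only section 2.3.1 fixes the high-risk window; section 2.3.2 is used here solely to show the order of the two periods.

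**DiD has a stated purpose.** Section 2.4.1 gives it as protection against structural differences left after balancing. This stands. Dropping both cost balancing and DiD from the main estimate would credit every unmeasured difference to high-risk status, and that is a debatable choice of estimand. DiD can therefore stay.

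**A mean comparison is already planned.** Section 2.4.1 does foresee testing mean differences in costs between the groups. As the section reads, however, the groups are those already balanced on healthcare costs, so the attenuation in Step 3 would carry over.

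**Stronger readings that the document does not support.** A reader might infer that A1 removes most of the excess cost. With a constant excess that needs r above about 0.5, and the article gives neither r nor cost levels. A reader might also infer that the removal follows from the contradiction. It does not: it belongs to the baseline reading only, and it comes from the cost balancing, since DiD subtracts nothing more once pre-year means are equal. Finally, a reader might infer that the cost-effectiveness ratio is compromised. Section 2.4.4 builds it on modules A2 and B1, and the A2 claims groups are selected under section 2.3.1.

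**Conclusion.** The contradiction is established from the text, and section 2.4.1 is wrong as written. Its wording makes follow-up events define the exposure while follow-up costs are the outcome, which tends to overstate the cost of illness. By how much depends on how many patients qualify only through such events and what those events cost; the article gives neither.

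The secondary point is conditional. With status set at baseline, cost balancing understates a persistent excess by a share of about r. The 20% to 80% range is an illustration for r from 0.2 to 0.8 and rests on an excess that is constant before and after index, equal variances and a linear pre/post relation. Real costs are skewed, so the relation is approximate. If there is no excess before index, nothing is lost. The consequence is confined to A1 unless its high-risk flag is carried into other modules, which the article does not say.

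**What to change.** 1. In section 2.4.1, replace observation period with baseline period in the sentence that lists the high-risk criteria, so that it matches section 2.3.1. No narrower window, such as codes before the index quarter only, should be introduced; that would match neither section.
2. Add one sensitivity analysis for A1: rerun the entropy balancing without healthcare costs among the balancing variables, and report the post-index difference in mean cost next to the planned DiD.
3. Describe the A1 DiD result as the change in excess cost after index, not as the total cost of illness, and state that balancing on pre-year cost may understate a persistent excess by an unknown share.

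The cost is one changed phrase, a sentence on interpretation, and one more weighting run on claims data already held. The sensitivity estimate does not difference out fixed unmeasured differences between the groups, which is why it belongs beside the DiD and not in its place.

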#### A2: direct and indirect costs in high-risk AF patients: LAAC procedure vs. best available medical care

2.4.2

To estimate direct and indirect costs, a population with maximum similarity to the EvaClosure study population will be selected from SHI claims data by statistical matching. Age, gender, comorbidity, CHA_2_DS_2_VASc and HAS-BLED scores, and medications (by classification) taken by control group patients will be used for matching of the populations, as observed by the quarter and year in which they and their statistical match meet the inclusion criteria. Matching will be verified using clinical trial data on medication, periprocedural events, (serious) adverse events, and comorbidities detected during follow-up visits of CLOSURE-AF trial patients. In the SHI population, healthcare costs of the LAAC group within a 2- and 5-year time frame will be estimated as the difference between the costs induced by the intervention group and the control group. Indirect costs will be evaluated based on the difference in the average length of incapacity to work documented per group, priced using industry-specific average employee compensation in Germany.

In addition, patient-reported information on health service utilization collected in the EvaClosure study (captured by the FIMA questionnaire as described in the trial data collection section) will be used to validate and supplement the claims data–based cost estimates. Moreover, information on non-medical direct and further indirect costs will be used to calculate societal costs that cannot be determined from SHI claims data. The FIMA questionnaire captures the use of services from general practitioners and specialists, outpatient treatment in hospitals, allied health services, nursing care, partial inpatient care, short-term care, and non-medical services such as housekeeping, assistance from family/friends, and use of other nursing care benefits, over the past three months (35). Similar questions encompass the utilization of inpatient treatment and rehabilitation services, medical devices, and day clinic services in the past 12 months, as well as sociodemographic and socioeconomic data. A validation study based on routine health insurance data (36) showed that resource consumption can be determined validly and reliably by the FIMA questionnaire. Patient-reported health service utilization will then be valued using the valuation rates calculated per observation year in this study, as described by Bock et al. (42) and Muntendorf et al. (43). To cover all components relevant to the target group of EvaClosure patients and to ensure that FIMA data collection is organizationally consistent with the clinical trial visit plan, the questionnaire was slightly modified by the authors of this paper^7^. In particular, the following modifications were made:
Because patients are surveyed with the FIMA every six months, questions on resource utilization covering a period of 12 months (see above) were modified to cover a period of six months.Information on sociodemographic and socioeconomic data as well as on drug utilization is collected in the CLOSURE-AF study. Therefore, questions covering these topics (e.g., on sex, age, marital status, and drug utilization within the last seven days) were waived.To estimate the indirect costs, two questions on unemployability (i.e., duration within the last six months and profession) were added.Using descriptive statistics, measures of location and dispersion will be compared for similarity. Difference-in-differences estimation will be applied to evaluate the incremental costs of the LAAC procedure by comparing the costs of services incurred by the intervention group and the control group. The time frame covers five years, comparing the average costs of both groups before and after the quarter of LAAC or first treatment with one of the pharmaceuticals defined as best medical treatment in the study design section.

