### Study design

2.1

EvaClosure is a longitudinal cohort study of adults with AF and high risk of stroke and bleeding, based on two independent study populations: an SHI claims data population and the EvaClosure population—a subpopulation of patients recruited in the CLOSURE-AF trial. There is no patient-individual linkage of the CLOSURE-AF trial data with the SHI claims data; however, since information from both data sources converge in the health economic evaluation, statistical matching is used to establish maximum similarity between both study populations.

Pseudonymized CLOSURE-AF trial data are used for matching, including study participants' demographic information (e.g., gender, age), medical history and comorbidities, therapy (treatment arm, medications), the CHA_2_DS_2_VASc and HAS-BLED scores, as well as periprocedural events, complications, and adverse events. A matched sample is drawn from the eligible SHI population, for which the utilization of healthcare services and corresponding costs are determined. The basis of data for the health economic evaluation and Markov modeling is supplemented by primary data on quality of life collected using the EQ-5D-5L instrument (33, 34) aggregated to QALYs, as well as information on further health resource usage captured by the validated and standardized FIMA^4^ questionnaire (35, 36) [modified version, see the section “Outcome measures and analyses” (A2) for details on the modifications]. The survey-based data are collected within the CLOSURE-AF trial every six months up to two years after patient inclusion.

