#### B2: health economic evaluation of LAAC

2.4.4

In module B2, a cost–utility analysis compares LAAC with best medical care. Based on the results of modules A2 and B1, the ICER up to five years after intervention is calculated, with QALYs serving as the main effect measure. The ICER determines the costs to SHI (perspective 1) as well as society (perspective 2) for an additional QALY gained. Depending on the underlying perspective, it will be calculated from direct and indirect costs in SHI claims data, supplemented by an analysis of FIMA data from EvaClosure study patients and QALYs derived from EvaClosure study patients as described in the previous section.

A Markov model adapted from the literature (46) will be employed to capture a lifetime horizon to assess long-term effects on costs and health-related quality of life. The transitions between different health states are linked by probabilities, and the Markov property assumes that the transition probabilities result exclusively from the current state (not from history). The parameters of the initial model (46) will be fine-tuned by SHI claims data estimates to capture probabilities for patients with high-risk AF, with risk estimates evaluated among matched populations of both treatment and control claims data groups. Further relevant parameters depending on the underlying Markov state (costs, utilities) will be derived from SHI claims data analyses and the EvaClosure primary data. Parameters that cannot be sufficiently quantified by one of these data sources may be extracted from the literature or health states may be coarsened. After completion of the CLOSURE-AF trial, clinical study results and comorbidity data of EvaClosure-enrolled patients will be used to adjust the final model.

To compare costs and health effects in different years, future costs and benefits will be discounted by an annual discount rate of 3% for SHI expenditures, indirect costs, and QALYs (47). The influence on the results will be systematically addressed in sensitivity analyses as described in the next section.

Figure 1 provides an overview of the study design, the main analyses, the two corresponding data sources, and matching criteria to ensure comparability of the SHI- and trial samples.

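### A2 and B2 match claims patients to the trial but state no step that directly balances the claims LAAC group against the claims control group

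*Protocol article*

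**What the plan says.** Protocol article, Study design (2.1): there is no individual linkage between trial and claims data, so "statistical matching is used to establish maximum similarity between both study populations". The trial data listed for this purpose include demographics, history, treatment arm, medications and the two risk scores. It continues: "A matched sample is drawn from the eligible SHI population, for which the utilization of healthcare services and corresponding costs are determined".

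Section 2.4.2 (A2) repeats the target, "a population with maximum similarity to the EvaClosure study population will be selected from SHI claims data by statistical matching", and names the variables: age, gender, comorbidity, CHA2DS2-VASc, HAS-BLED and medication class, the last worded as "medications (by classification) taken by control group patients will be used for matching of the populations". Pre-index healthcare cost is not on the list. The match is then verified against trial data. Healthcare costs of LAAC in the claims data are "estimated as the difference between the costs induced by the intervention group and the control group", and later in the section: "Difference-in-differences estimation will be applied to evaluate the incremental costs of the LAAC procedure". Table 2 gives the same design for the A2 claims population.

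Section 2.4.1 (A1) handles its own two-group contrast differently. Entropy balancing is used for similarity in age, gender, morbidity and "healthcare costs between the high-risk group and the control group without the high risk at baseline". Difference-in-differences is then added for unobserved differences left over after balancing.

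Section 2.4.4 (B2) takes the high-risk transition probabilities from claims estimates, "with risk estimates evaluated among matched populations of both treatment and control claims data groups".

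**The concern.** The matching answers one question: do the claims patients look like the trial patients? The A2 and B2 estimates need a second: are the claims LAAC and claims control patients comparable with each other? Success on the first does not secure the second, because treatment in the claims data was not randomised.

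The article itself shows why the groups may differ. The Background (1.1) says guidelines recommend considering LAAC in selected patients with contraindications to long-term anticoagulation. Section 2.3.1 defines claims controls as high-risk patients treated with a NOAC or VKA. Suitability for anticoagulation therefore helps to decide who is in which group. Prior anticoagulant use and recent bleeding admissions are not in the A2 variable list, and the risk scores can carry them only in part.

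The cost difference feeds the ICER up to five years. The transition risks feed the lifetime model.

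**Working it through.** No stated figure underlies this point, so there is none to reproduce. The check sets the sections side by side and then uses a simulation on assumed inputs to see which parts of the estimate are exposed.

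**Side by side**

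- *A1:* the contrast is high-risk versus not high-risk. The two groups are balanced against each other, including on baseline costs, and difference-in-differences follows.
- *A2:* the contrast is claims LAAC versus claims control. The stated matching is claims to trial, without baseline cost, and difference-in-differences follows.
- *B2 transition risks:* the contrast is the same as in A2. Both groups are called matched, but not to what. Table 2 lists difference-in-differences in the B2 row, yet 2.4.4 does not attach it to the transition risks.

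**Illustration (all inputs assumed, true LAAC effect zero)**

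- 400,000 patients with two independent standard normal covariates: x, which is matched, and u, which is not.
- Treatment: logit P(LAAC) = −1 + 0.5x + 0.5u.
- Cost before index: 1000x + 1000u + noise (SD 500).
- Cost after index: cost before + 500 + k(x + u) + noise (SD 500), with k = 0 (parallel trends) or k = 300 (trends depend on covariates).
- Event: logit risk = −2.5 + 0.4x + 0.4u.
- Trial target: x with mean 0.3 and variance 1.

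Each entry is LAAC minus control, so any departure from zero in the cost and risk columns is bias.

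| Matching | Gap in x | Gap in u | Cost, k = 0: simple / DiD | Cost, k = 300: simple / DiD | Event risk |
|---|---|---|---|---|---|
| None | 0.456 | 0.453 | 908 / −1 | 1181 / 273 | 2.8 points |
| All claims patients matched to trial together | 0.456 | 0.452 | 906 / −2 | 1181 / 272 | 3.2 points |
| Each claims group matched to its own trial arm | 0.000 | 0.474 | 469 / −3 | 615 / 144 | 1.6 points |

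The cost columns follow from the gaps, up to noise. The simple contrast at k = 0 is about 1000 × (gap in x + gap in u): 1000 × (0.456 + 0.452) = 908 for pooled matching and 1000 × 0.474 = 474 for arm-by-arm. Difference-in-differences is about k × (gap in x + gap in u). That is 0 at k = 0. At k = 300 it is 300 × 0.908 = 272 for pooled matching and 300 × 0.474 = 142 for arm-by-arm.

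**Reading**

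1. Matching to the trial as a whole leaves the gap between the claims groups where it was.
2. Matching each group to its own arm closes the gap on the matched variable but not on the unmatched one.
3. Difference-in-differences removes constant cost differences under either form of matching, but not differences in trend.
4. The event-risk contrast has no before-period correction, so it keeps bias under either form.

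Parallel trends cannot be taken for granted here. In A2 the index quarter is the LAAC quarter in one group and the quarter of first best-medical-care treatment in the other, which are different points in the care pathway.

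**The case against.** The strongest reply is that the plan already corrects for much of this.

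- **Difference-in-differences is specified for costs** in 2.4.2 and Table 2. This stands. A reader might infer from the matching text that the cost difference is uncorrected; the documents do not support that.
- **The trial arms were randomised 1:1, and treatment arm is among the data listed for matching in 2.1.** If each claims group is matched to its own arm, the listed variables are balanced indirectly. This also stands, so it would be wrong to say that the groups are never balanced. But arm-by-arm matching is suggested, not stated. It would leave unlisted variables alone, and EvaClosure is a consenting, partly retrospectively enrolled subset of the randomised trial.
- **Both claims groups meet the same bleeding-risk entry criteria, and HAS-BLED is matched.** This narrows the gap in bleeding history without closing it.
- **The B2 wording may mean that the two groups are matched to each other.** It may. The text is ambiguous rather than silent.
- **The transition risks do not rest on claims alone.** A literature model is the starting point, CLOSURE-AF results adjust the final model, and 2.5 adds a re-parameterised sensitivity analysis. This limits the damage but does not replace a sound claims estimate.
- **Covariate lists and balance diagnostics are often left to a fuller document.** That is fair for detail. Here, however, the article states the matching target and its variables, and that target does not by itself serve the contrast.

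A reader might also infer that matching means drawing a small set of counterparts to the trial patients, discarding most claims patients and leaving event risks very imprecise. The article gives no matching ratio or sample size, and in A1 it classes a weighting method as statistical matching, so this cannot be concluded.

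**Conclusion.** The point holds in a limited form. A2 and B2 state alignment of the claims population with the trial population, but no direct balancing of the two non-randomised claims groups whose difference is estimated, although A1 does this for its own contrast. For costs, the exposure is to differing trends. For the claims-based transition risks it is wider, because no before-and-after adjustment is described and the matching target is unclear.

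The size cannot be derived from the documents. The illustration shows where bias can remain, not how large it would be here. It assumes that some drivers of treatment choice lie outside the matching list and affect cost trends or event risk. The article makes the first part plausible but does not quantify either. The change is worth making because the better method is already in the plan.

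**What to change.** 1. In A2 and B2, apply A1's entropy balancing to weight the eligible claims LAAC and claims control patients to one common target: the baseline covariates of the EvaClosure patients, pooled over both arms.
2. In the same step, balance the two claims groups on pre-index healthcare costs, prior admissions and bleeding history. Add prior anticoagulant use only where overlap allows. If controls are indexed at their first-ever treatment, they will have little or no prior use, balance on it may be unattainable, and that should be reported as a limitation.
3. Use the same weights for the cost difference-in-differences and for the transition risks, and say in 2.4.4 what the groups are matched to.
4. Use control-arm medication class only to set the treatment mix within the control group.
5. Report standardised differences between the two weighted claims groups, not only between claims and trial.

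The cost is analysis wording and programming, with no new data. The downside is some loss of effective sample size from the weighting, which should be reported.
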